### Participant timeline {13}

The participant time lime is described in Table 1.

**Table 1 Tab1:** Schedule of enrollment, intervention and assessment

Participant timeline	At arrival	During treatment	After treatment	1–12 h after treatment	24 h after treatment	48 h after treatment	Hospital discharge	3 months after treatment
**Enrolment**								
Eligibility assessment			**X**					
Informed consent			**X**					
Allocation			**X**					
**Interventions**								
Early extubation (< 6 h)				**X**				
Delayed extubation (6–12 h)				**X**				
**Assessments**								
Baseline variables	**X**							
Laboratory testing	**X**				**X**		**X**	
Brain image	**X**				**X**			
NIHSS score	**X**				**X**	**X**	**X**	
mRS score	**X**						**X**	**X**
TICI reperfusion		**X**						
Length of hospital and ICU stay							**X**	
Complications associated with VM		**X**	**X**	**X**	**X**	**X**	**X**	
Complications during hospital stay				**X**	**X**	**X**	**X**	

*ICU* intensive care unit, *mRS* modified Rankin Scale (ranges from 0 (no symptom) to 6 (death)), *NIHSS score* National Institutes of Health Stroke scale (range 0–42, higher scores indicate more severe neurologic deficits), *TICI reperfusion* thrombolysis in cerebral infarction, TICI 2b-2c-3 indicate successful reperfusion, *MV* mechanical ventilation

### Sample size {14}

We aim to compare neurological functional status at 90 days according to the modified Rankin scale (mRS), of patients with stroke who underwent endovascular thrombectomy with satisfactory results and who underwent early extubation (< 6 h) compared to delayed extubation (6–12 h). Efficacy will be assessed with the proportion of patients with functional independence (mRS scale ≤ 2).

A previous observational study [20] reported that 55.5% of patients achieved an mRS score of ≤ 2 after receiving early extubation (mechanical ventilation for less than 6 h), compared to 33.9% when extubation was delayed (mechanical ventilation for more than 6 h). In present trial, we hypothesize that early extubation, compared with delayed extubation, is associated with a better functional outcome 3 months after endovascular thrombectomy under general anesthesia for acute ischemic stroke. We have decided to set the level of significance at 5% (*α* = 0.05), with a power of 80% (*β* = 0.80), and to use a bilateral test (c = 2). We will work with two independent samples and both groups will be balanced (w1 = 0.5). Considering an expected percentage of losses is 5.00%, it would be necessary to include 87 individuals in each group, totaling 174 patients in the study. Depending on the course of the study, an interim analysis will be conducted when 70% of the recruited sample is reached, if deemed appropriate by the research team.We hypothesized that early compared with delayed extubation is associated with a better functional outcome 3 months after endovascular thrombectomy treatment under general anesthesia for acute ischemic stroke.

### Recruitment {15}

Patients admitted to the ICU with acute ischemic stroke due to a proximal occlusion of the anterior circulation who meet the inclusion criteria will be recruited by trial investigators. Eligible patients, or their legal representatives if the patient cannot understand information due to an underlying disease, will receive both written and oral information. They will be included in randomization after investigators have obtained informed written consent. Patients are expected to be enrolled over a 3-year period starting in April 2023. To date (February 2024), 70 patients have been randomized in the trial.

## Assignment of interventions: allocation

### Sequence generation {16a}, concealment mechanism {16b}, implementation {16c}

Randomization will be performed immediately after the patient is admitted to the ICU. Enrolled participants will be randomized in a 1:1 ratio for early or delayed extubation. To ensure balance between the two groups, a computer-generated random block number table will be used (blocks of 8). A designated staff member, not involved in extubation, anesthesia management, or follow-up will handle recruitment and generate the allocation randomization sequence. The staff member will implement the allocation sequence through opaque, sealed, and stapled envelopes.

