## Methods: participants, interventions, and outcomes

### Study setting {9}

The EDESTROKE trial will be conducted in one university Hospital in Spain (University Clinical Hospital of Santiago de Compostela, Galicia, Spain).

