### Who will take informed consent? {26a}

Trial investigators will identify consecutive patients admitted to the ICU with acute ischemic stroke due to a proximal occlusion of the anterior circulation, who meet the inclusion criteria. Eligible patients or their legal representatives if the patient cannot understand information due to an underlying disease will receive written and oral information and will be included in randomization after investigators have obtained informed written consent. Once patients are extubated and if their medical condition allows them to understand the information, they will be given the option to either continue participating in the study or withdraw themselves from it.

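### As written, one staff member recruits, generates the sequence and runs the envelopes, while other sections give enrolment to investigators; the roles must be reconciled and separated, and the single block size of 8 adds some predictability

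*Protocol article*

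**What the plan says.** Under Sequence generation {16a}, concealment mechanism {16b}, implementation {16c}, the protocol article says that a designated staff member, who takes no part in extubation, anesthesia or follow-up, "will handle recruitment and generate the allocation randomization sequence". It continues: "The staff member will implement the allocation sequence through opaque, sealed, and stapled envelopes". On the method it says that "a computer-generated random block number table will be used (blocks of 8"), and that "Enrolled participants will be randomized in a 1:1 ratio for early or delayed extubation". No other block size and no stratification is given.

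Other sections describe enrolment differently:

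- Recruitment {15}: stroke patients admitted to the ICU "who meet the inclusion criteria will be recruited by trial investigators", and investigators obtain written consent before randomization.
- Who will take informed consent? {26a}: "Trial investigators will identify consecutive patients admitted to the ICU with acute ischemic stroke".
- The oversight section {5d, 21a}: medical researchers oversee screening and inclusion.

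The setting is a single centre: "The EDESTROKE trial will be conducted in one university Hospital in Spain". Recruitment {15} also reports that 70 patients had been randomized by February 2024, with enrolment continuing.

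**The concern.** Allocation concealment requires that whoever decides whether a patient enters the trial cannot know the next assignment. A sealed envelope hides the assignment from others, but not from the person who produced the list. The allocation section separates this staff member from treatment and follow-up, which limits performance and detection bias. It does not separate them from enrolment.

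There is some room for discretion at entry. One exclusion turns on whether a lung condition might call for ventilatory support, and consent depends on whether and when a patient or proxy is approached. Someone who knew the next arm could enrol or pass over a patient according to expected readiness for extubation. The Background and the Discussion give infarct size, NIHSS and neurological status as reasons why observational comparisons of extubation timing are hard to interpret. Selection at enrolment could bring that same confounding back. Blinded mRS assessment and intention-to-treat analysis do not correct it, because it happens before randomization.

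The single printed block size is a separate and smaller route to the same problem.

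**Working it through.** **1. Who does what, by section**

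| Task | Allocation {16a–c} | Other sections |
|---|---|---|
| Identify and screen | not stated | trial investigators {26a}; medical researchers {5d, 21a} |
| Recruit | designated staff member | trial investigators {15} |
| Obtain consent | not stated | investigators {15} |
| Generate the sequence | designated staff member | not stated |
| Implement the envelopes | designated staff member | not stated |

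This allows two readings. If the allocation section holds, an enroller wrote the list and can know every coming assignment. If the other sections hold and those investigators cannot see the list, the envelopes conceal it from them, and only block predictability remains. The article does not settle which applies.

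**2. The trial size used as denominator**

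The inputs come from Sample size {14}: 55.5% against 33.9%, two-sided 5%, 80% power, 1:1, 5% losses. With pooled variance and no continuity correction:

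n = [1.96·√(2·0.447·0.553) + 0.8416·√(0.555·0.445 + 0.339·0.661)]² / 0.216² = 3.825 / 0.04666 ≈ 82 per group.

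82 / 0.95 = 86.3, so 87 per group and 174 in total. The stated figure reproduces, and the point does not depend on it. Patients remaining after the first 70: 174 − 70 = 104.

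**3. Predictability from a block of 8 at 1:1 (m = 4 per arm)**

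The observer is assumed to know the block size, the block boundaries and every earlier assignment.

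- *Certain assignments.* These are the ones left after one arm is used up. The expected number of early assignments after the last delayed one is m/(m+1), and likewise with the arms swapped. The total is 2m/(m+1) = 8/5 = 1.6 per block, and 1.6 / 8 = 20%.
- *Best guess.* Always guessing the arm with more places left gives m + ½·(2^(2m)/C(2m,m) − 1) = 4 + ½·(256/70 − 1) = 5.33 correct of 8, or 66.6%, against 50% under full concealment.
- Enumerating all 70 arrangements of the block gives the same two values.
- For comparison, the certain share is 33% for blocks of 4 and 14% for blocks of 12.

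**4. Applied to the patients who can still be protected**

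0.20 × 104 = 20.8, about 21 assignments.

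**The case against.** The strongest reply is that a concealment failure has not been shown. Three sections give identification, consent or inclusion to investigators or medical researchers. Only one clause in the allocation section says otherwise, and handling recruitment there could mean the logistics of entering a patient who has already consented. There are also safeguards. Patients are to be consecutive, randomization follows immediately on ICU admission, and most eligibility items are recorded facts (occlusion site, NIHSS, TICI, prior mRS, place of intubation). The Research Methodology Unit also reviews screening forms at regular intervals under the auditing section {23}.

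Much of this stands, and it rules out some stronger readings:

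- *Allocation is open to whoever enrols, and every assignment is predictable.* This follows only if the list-holder takes part in enrolment, which the documents leave in conflict.
- *ICU staff see every allocation.* The article does not say so. The blinding section says that a trial team member who assesses ICU outcomes is not blinded. Extubation time is visible at the bedside, but it is an imperfect guide to assignment because some patients may not be extubated in their window.
- *About 35 of 174 assignments are exposed.* This is 20% of the whole trial (34.8). The article that prints the block size already reports 70 patients randomized, and a change can only protect the rest.
- *Selection has occurred.* No document shows this. Predictability is an opportunity for bias and does not measure it.

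The reply does not remove the wording of the allocation section. The safeguards limit selection, but do not exclude it if the person with the list also recruits.

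**Conclusion.** The point holds in conditional form. The allocation section assigns recruitment, sequence generation and envelope implementation to one person, and under that procedure allocation is not concealed from that person. Confidence is high about the wording and the conflict between sections. Whether concealment fails in practice depends on whether the list-holder takes part in enrolment, which the article does not resolve.

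The block size is secondary. The 20% certain share (about 21 of roughly 104 remaining patients) and the 67% best-guess rate are upper bounds. They require an observer who tracks all past assignments and knows where each block starts. They also assume the total of 174 given in Sample size {14}. No effect on the primary comparison can be estimated from the documents.

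**What to change.** 1. Reconcile the consent {26a}, recruitment {15}, allocation {16a–c} and oversight {5d, 21a} sections into one description in which nobody who screens, consents or enrols generates the list or can see it. If practice already works this way, correcting the text is enough for this part.
2. For remaining patients, have someone independent of enrolment generate and hold a new sequence with randomly varying, undisclosed block sizes. The Research Methodology Unit is one candidate if it agrees; the article gives it only a review role at present.
3. Use sequentially numbered envelopes, opened only after eligibility and consent are recorded. The inclusion criteria also allow consent to follow in an emergency, so in those cases the basis for inclusion should be recorded before opening.
4. State in the trial report who generated the sequence and who enrolled the patients randomized before the change. Do not use a comparison of results before and after the change as a test for bias. At roughly 70 against 104 patients, in a trial sized for 80% power on all 174, it could neither show nor exclude selection.

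The cost is a short amendment, a new envelope set and some time from whoever holds the list. The sample size does not change.

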## Assignment of interventions: blinding

### Who will be blinded {17a}, procedure for unblinding if needed {17b}

The primary outcome (mRS assessed 90 days after the endovascular thrombectomy) and secondary outcomes such as NIHSS at day 1, day 2, and at hospital discharge, as well as mRS at hospital discharge, complications during Hospital stay outside the ICU, and hospital length of stay, will be assessed by a neurologist from the trial team who is blinded to the randomization group. Complications during ICU stay, duration of mechanical ventilation, and complications associated with mechanical ventilation will be assessed by a trial team staff member who is not blinded.

## Data collection and management

### Plans for assessment and collection of outcomes {18a}, plans to promote participant retention and complete follow-up {18b}, data management {19}, confidentiality {27}

Pseudonymized data will be collected and managed in an electronic case report form (eCRF) specifically designed and validated for this purpose. Access to data will comply with local, national, and European Union data protection regulations. Each patient will be assigned a unique trial identification number, which will be disassociated from their personal information. The database will be protected by encryption software. Only the investigators and research team will have access to any protected health information of study participants and any study data. Any protocol deviations will be recorded on the eCRF, and a clinical research assistant will ensure that all protocol deviations and adverse events are recorded in the database. The following data will be registered:

Baseline characteristics and intraoperative data will include:Demographic data (age, height, weight, gender, and body mass index)American Society of Anesthesiologists physical statusSignificant comorbidities (cardiovascular, respiratory, neurological, cancer, atrial fibrillation, smoking, statin use, antiplatelet and anticoagulant treatments)NIHSS score at admissionTime of symptom onset, time of arrival at the hospital, time of first image for diagnosis, time of arterial puncture, time of tracheal intubation, time of recanalizationType of anesthesia (general anesthesia vs. sedation)Modified Thrombolysis in Cerebral Infarction (mTICI) scoreNeed for norepinephrine during endovascular treatmentIntraoperative complications (hypotension, hypertension, duration of procedure, stroke localization, intravenous fibrinolysis if applicable)Type of endovascular stroke treatment (direct aspiration, stent retriever, angioplasty, etc.)Procedural-related complications.

ICU data:Duration of mechanical ventilation (hours)pO2 at ICU admissionTime of extubationNeed for norepinephrine during mechanical ventilation and after mechanical ventilationMechanical ventilation complications (pneumothorax, pneumonia, etc.)Duration of ICU stay (hours)Complications during ICU stay (reintubation, infection, prolonged mechanical ventilation (> 48 h), prolonged ICU stay (> 48 h), ICU mortality, and other complications)

Hospital data:NIHSS score on day 1, day 2, and at hospital dischargemRS at hospital discharge and 3 months after endovascular treatmentComplications during hospital stayDuration of hospital stay (days)

### Plans for collection, laboratory evaluation, and storage of biological specimens for genetic or molecular analysis in this trial/future use {33}

Not applicable as no biological samples will be collected for future analysis.

## Statistical methods

### Statistical methods for primary and secondary outcomes {20a}

#### Description of the patient groups at baseline

The baseline characteristics of all patients will be described. Categorical variables will be reported as absolute numbers (*n*) and percentages and quantitative variables as either means (standard deviation) or medians (25th percentile–75th percentile). Data will be analyzed using chi-square and Wilcoxon rank-sum test (or paired samples *T* test) as appropriate. Pearson or Spearman correlation coefficient will be calculated to compare patient specifics between groups at the baseline. Normality will be calculated with Kolmogorov–Smirnov test with Lilliefors correction.

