### Trial design {8}

The EDESTROKE trial is an investigator-initiated, single-center, prospective, parallel, evaluated blinded, superiority, randomized controlled trial.

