#### Analysis of the secondary outcomes

The techniques that will be used to answer the secondary objectives will be fundamentally statistical inference techniques. The selection of each of them will depend on the nature of the variables involved, as well as their adjustment to normality.

All these analyses will be carried out with the statistical program SPSS 19.0 and those whose *p*-value is lower than 0.05 will be considered statistically significant values.

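### The baseline section names a paired t test and correlation coefficients to compare two independent, unmatched arms; both need rewording (minor)

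*Protocol article*

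**What the plan says.** All references are to the protocol article.

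- **Description of the patient groups at baseline** (under Statistical methods {20a}) lists the tests: "Data will be analyzed using chi-square and Wilcoxon rank-sum test (or paired samples" t test), to be used as appropriate. The paired test stands in parentheses as the alternative to the rank-sum test. The next sentence reads: "Pearson or Spearman correlation coefficient will be calculated to compare patient specifics between groups at the baseline".
- **Trial design {8}**: "The EDESTROKE trial is an investigator-initiated, single-center, prospective, parallel, evaluated blinded, superiority, randomized controlled trial".
- **Sample size {14}**: "We will work with two independent samples and both groups will be balanced (w1 = 0.5").
- **Sequence generation {16a}**: "Enrolled participants will be randomized in a 1:1 ratio for early or delayed extubation". A table of random blocks of eight is used, and no matching is described.
- **Analysis of the secondary outcomes** names no test. It says only that the choice "will depend on the nature of the variables involved, as well as their adjustment to normality".

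**The concern.** A paired t test analyses within-pair differences, so each observation in one arm must have a designated partner in the other. Nothing in this design supplies partners. If the sentence were followed literally, the software would pair patients by their order in the file. The p-value would then depend on that order, and the test would fail when the arms have different numbers of observations.

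The correlation sentence is a separate fault. Pearson and Spearman coefficients describe how two variables vary together in the same patients. The stated purpose is to compare patient characteristics between the groups, and a coefficient between two characteristics does not do that.

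What is at stake is whether the baseline comparison can be reproduced and interpreted. The article names no independent-samples t test anywhere, so it offers no correct parametric two-group test to use instead.

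**Working it through.** **1. Does the protocol's own arithmetic treat the arms as unpaired?**

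Inputs from Sample size {14}: success rates 55.5% and 33.9%, two-sided alpha 0.05, power 80%, losses 5%. The formula is the one for two independent proportions, with pooled variance under the null and no continuity correction:

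n = [z₀.₉₇₅ √(2p̄(1−p̄)) + z₀.₈₀ √(p₁(1−p₁) + p₂(1−p₂))]² / (p₁−p₂)²

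- p̄ = (0.555 + 0.339)/2 = 0.447
- First term: 1.960 × √(2 × 0.447 × 0.553) = 1.378
- Second term: 0.842 × √(0.2470 + 0.2241) = 0.578
- n = (1.378 + 0.578)² / 0.216² = 81.98, so 82 per arm
- Allowing for losses: 82/0.95 = 86.3, so 87 per arm and 174 in total

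This is the stated figure. The sample size was therefore reproduced with an unpaired formula, in line with the text of that section.

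**2. Is there any pairing to use?**

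Trial design {8} gives a parallel trial, and Sequence generation {16a} gives 1:1 allocation in blocks of eight. Blocks balance numbers but do not create matched pairs. The baseline section describes no within-patient comparison either. The rank-sum test, to which the paired test is offered as alternative, is itself an independent-samples test, so the sentence is inconsistent within itself.

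**3. What would the paired test do to unpaired data?**

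The paired statistic divides the mean difference by √[(s₁² + s₂² − 2r s₁s₂)/n], where r is the sample correlation across the pairs. With similar variances this gives t(paired) ≈ t(independent)/√(1−r). In independent arms r is pure noise from the row order, with standard deviation about 1/√(n−1) = 1/√86 = 0.108 at 87 per arm.

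One simulated normal data set with 87 per arm had t = 2.489 (absolute value) and p = 0.0138 on the independent test. Taking r at ±1.96 × 0.108 = ±0.21:

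- r = +0.21: 2.489/√0.79 = 2.80, p about 0.006 on 86 df
- r = −0.21: 2.489/√1.21 = 2.26, p about 0.026 on 86 df

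Simulation agrees. Over 5,000 random orderings of one arm the paired p had a central 95% range of 0.0064 to 0.0258 and extremes of 0.0019 and 0.0356.

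**4. Does it raise the false-positive rate?**

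No. In 10,000 simulated null data sets with 87 per arm, the paired test rejected in 4.6% and the independent test in 4.7%. The fault is an arbitrary result, not a biased one.

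**5. Can the arms differ in size?**

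Yes. A total of 174 is 21 full blocks of eight (168) plus 6 patients. If each block holds four of each arm, the last 6 can split 4:2. Missing values or the expected 5% losses can separate the numbers further. With 87 against 86 values the paired test returned an error.

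**6. Could the correlation be a valid comparison?**

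Only in one form. The Pearson correlation of a variable with a 0/1 arm indicator gave p = 0.0138 in the same data set, identical to the independent t test. That use only restates the t test, and the baseline section does not describe it.

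**The case against.** The strongest reply is that this is a slip of one word. The test stands beside the rank-sum test, the article elsewhere says "We will work with two independent samples", and the list is qualified by an as-appropriate clause. A competent analyst would run the independent test. That is probably what was meant, and it is a good reason to rate the point low. It does not remove the error: the clause selects among the tests listed, and the only t test listed is never appropriate for comparing these arms.

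Three stronger readings may tempt a reader, and the document supports none of them.

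- **That the paired test is prescribed for the continuous secondary outcomes.** A reader might infer this because it is the only parametric two-group test of means named. But the sentence belongs to the baseline section, and the secondary-outcome section does not refer back to it and has its own selection rule. Naming no test there is a detail commonly left to an analysis plan. The error reaches NIHSS or length of stay only if the analyst carries the baseline wording across.
- **That significance becomes close to a coin toss.** If simulated data (82 per arm) are fixed so that the independent p is exactly 0.050, about 45% of random pairings fall below 0.05. That figure follows from placing the data on the threshold. It does not describe typical behaviour, and the null error rate is unchanged.
- **That a correlation can never compare arms.** This is too absolute, given the arm-indicator case in step 6 of the working. The defect is the use the text describes.

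**Conclusion.** The point holds as a wording error in the baseline methods. Both named methods conflict with the article's own description of a parallel, unmatched trial with independent samples. Followed literally, the paired test gives a p-value that depends on row order, or no result when the arms are unequal, and the correlation does not answer the question set for it.

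Its reach is limited. The primary analysis (regression with a relative risk) and the 174-patient sample size do not depend on it, the type I error rate is not inflated, and chi-square and rank-sum in the same sentence are valid. The p-value range rests on one simulated data set of normal values with 87 per arm and random ordering; it shows the mechanism and does not predict any trial result.

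Severity: minor.

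**What to change.** In the baseline section, replace the paired-samples t test with the independent-samples t test and say whether Student's or Welch's version is meant; either fits the design. Delete the correlation sentence, or limit it to associations between variables and drop the claim that it compares the groups.

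Replacing baseline p-values with standardised differences is a reasonable option but is not needed to correct this error. If it were adopted, the t test would have no role left in that section.

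The cost is two sentences. No stated figure changes: the sample size stays at 87 per arm because it already assumes independent samples. No data collection is affected, and the article reports recruitment still under way, so the correction can be made before analysis.
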